### Trial Schedule

All patients who provide consent are assessed for eligibility by neurosurgeons specializing in pain management. Eligible participants will be randomly allocated to 1 of the 3 groups and undergo baseline evaluations, including demographic and clinical characteristics. The intervention is administered once a week for 8 weeks (Figure 2). This schedule was determined based on previous rTMS studies, which showed that intermittent stimulation—such as weekly sessions—provides significant pain relief for between 4 and 8 weeks or sessions, after which the effect tends to plateau [17-20]. Participants will be asked to record a pain diary from 1 week prior to the intervention until 1 week after completion at week 8. The NRS for pain and paresthesia (*shibire* in Japanese), along with the Short-Form McGill Pain Questionnaire version 2 (SF-MPQ-2) [21], will be assessed at baseline, immediately after each intervention, and at follow-up visits. Additional measures—including the Brief Pain Inventory (BPI) [22], EQ-5D-5L [23], Hospital Anxiety and Depression Scale (HADS) [24], Pain Catastrophizing Scale (PCS) [25,26], Pain Self-Efficacy Questionnaire (PSEQ) [27], MMSE, quantitative sensory testing (QST), motor cortical excitability, and the *shibire* questionnaire (validated by our group; [name], unpublished data, October 2024) [28]—will be assessed at baseline and immediately after the final intervention at week 8. At the end of the study, Patient Global Impression of Change (PGIC) and blinding assessments will be collected. Adverse events will be monitored continuously from the start of the intervention until follow-up visits at weeks 12 and 16 or until study discontinuation. Potential adverse events associated with TUS will be explained to participants during the informed consent process. In addition, at each treatment session, participants will be asked whether they have experienced any new symptoms or deterioration. The detailed schedule is shown in Table 1.

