
Treatment will be administered with the participant seated comfortably in a reclining chair. Ultrasound gel will be applied to the scalp, gel pad, and transducer, with all visible air bubbles carefully removed. The transducer will then be affixed to the scalp via a gel pad to ensure complete contact. To maintain blinding, participants will not be shown the TUS device interface, and white noise will be delivered through earphones during stimulation to mask any device sounds. All interventions will be performed under the supervision of investigators who are also neurosurgeons specialized in neuromodulation. In the sham stimulation group, the transducer will be placed over M1, but no ultrasound will be emitted (0 W output), with the same device setup and procedures as in the active stimulation groups. Because TUS is not typically associated with distinct sensory perceptions during stimulation, participants are not expected to distinguish active from sham stimulation based on treatment sensation alone. A single sham condition will be used as a common control group for both active stimulation targets. Because participants will be assigned to only 1 treatment arm throughout the study and will not be exposed to multiple stimulation targets, differences in transducer location will not be expected to substantially affect participant blinding.

To minimize confounding effects, the initiation of new treatments for NP and alterations to existing regimens will, in principle, be prohibited from the time of enrollment until week 8. The use of rescue analgesics will be permitted during the study provided that it does not substantially deviate from the participant’s preintervention medication regimen. Participants will be instructed to maintain their existing analgesic treatment whenever possible throughout the study period. Exceptions may be permitted when required to ensure participant safety.

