#### Quantitative Sensory Testing

This test is conducted using thermal and vibration stimulators (TSA-II and VSA-3000; Medoc) based on published methods [36]. Warm, cold, heat pain, cold pain, and vibration detection thresholds will be assessed on the volar forearm or calf of the painful side. Each session includes 2 practice and 4 formal measurements. These assessments will be performed only when the stimulation target is the upper or lower limb.

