#### Motor Cortical Excitability

Evaluated using single- and paired-pulse TMS with a figure-8 coil of 70 mm, 2 Magstim 200^2^ stimulators, and a Magstim BiStim^2^ module. MEPs will be recorded from the first dorsal interosseous muscle on the painful side (Brainsight MEP module; Rogue Research Inc) elicited via contralateral M1 stimulation. Measures include resting motor threshold (RMT), short-interval intracortical inhibition, intracortical facilitation, and cortical silent period [37]. The motor hot spot is defined as the site eliciting the largest MEP and RMT as the lowest stimulation intensity evoking MEPs of 50 μV or more in at least 5 of 10 trials. Paired-pulse TMS will use a conditioning stimulus at 80% RMT and a test stimulus at 120% RMT, with interstimulus intervals of 2 ms (short-interval intracortical inhibition) and 15 ms (intracortical facilitation) plus control stimuli alone. Each stimulus will be delivered 10 times in a randomized order. The cortical silent period will be measured 10 times under 10% to 20% maximum voluntary contraction at 130% RMT, with an intertrial interval of at least 5 seconds.

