#### Adverse Events

These are defined as any unfavorable or unintended sign, symptom, or illness occurring in a participant regardless of causal relationship to the study. Worsening of preexisting conditions will also be considered adverse events.

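### Adverse-event collection opens at the first ultrasound session, so events from the baseline TMS and sensory testing fall outside it

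*Protocol article*

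**What the plan says.** Trial Schedule sets the collection window: "Adverse events will be monitored continuously from the start of the intervention until follow-up visits at weeks 12 and 16", or until the participant discontinues the study. Table 1 matches this. The adverse-event row is ticked at weeks 1 to 8, 12 and 16 and is blank in the two columns before week 1. Active questioning about new or worsening symptoms is described for each treatment session.

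Two of the study's own test procedures come earlier. Trial Schedule lists "quantitative sensory testing (QST), motor cortical excitability" among measures that "will be assessed at baseline and immediately after the final intervention at week 8", and Table 1 ticks both at week 0. Motor cortical excitability is "Evaluated using single- and paired-pulse TMS with a figure-8 coil of 70 mm"; the section also describes a silent-period series at 130% of resting motor threshold. For sensory testing, "Warm, cold, heat pain, cold pain, and vibration detection thresholds will be assessed" on the forearm or calf of the painful side, only in participants with limb pain.

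Three further statements bear on the interval before session 1. Trial Schedule names random allocation before the baseline evaluations. Participants applies its withdrawal criteria after enrollment, the first being unacceptable risk because of an adverse event. Interventions says that new or altered neuropathic pain treatment is, in principle, "prohibited from the time of enrollment until week 8".

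**The concern.** Safety is part of the stated objective. A trial that asks participants to undergo brain stimulation for measurement and heat-pain and cold-pain testing would normally want to know what those procedures did, at baseline as well as at week 8. Here the same two procedures lie inside the window at week 8 and outside it at week 0, and the article gives no reason for the difference.

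Two things are at stake. First, an event that follows the baseline tests or arises in the preintervention week has no scheduled place to be recorded. If it leads the participant to leave before session 1, the question asked at sessions never reaches that person. Second, a symptom reported at week 1 has to be classed as new or as already present. For symptoms outside the baseline scales there is no scheduled pre-session record to compare with, and the investigators making the judgement know the allocation.

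**Working it through.** The article gives no figure on this point to reproduce, so the check is a timeline.

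| Interval | What happens | Adverse-event row in Table 1 |
|---|---|---|
| Week 0 | Baseline scales; TMS battery; sensory testing if limb pain. Allocation is named before these in Trial Schedule. | Blank |
| Preintervention period | Daily pain diary for 1 week; the restriction on treatment changes already applies, having begun at enrollment | Blank |
| Weeks 1 to 8 | Weekly sessions; TMS and sensory testing repeated at week 8 | Ticked |
| Weeks 12 and 16 | Follow-up | Ticked |

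**Step 1: is the start date ambiguous?** No. The text and Table 1 agree on it.

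**Step 2: what lies before it?** The week-0 TMS battery, week-0 sensory testing in those with limb pain, and at least the one-week diary period.

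**Step 3: does another rule use that interval?** Yes. The withdrawal criteria apply from enrollment and the first rests on an adverse event. A participant can thus be withdrawn for an event at a time when none is scheduled to be collected.

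**Step 4: who is never asked?** Someone who leaves before session 1. That person is also outside the full analysis set, which requires at least one session. That set is defined for efficacy; the article describes no separate safety set, which may be in a document not shown.

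**Step 5: what pre-session symptom record exists?** Pain (NRS, SF-MPQ-2, BPI and the diary), *shibire* where present, mood (HADS), health status (EQ-5D-5L) and cognition (MMSE). Symptoms outside these measures have no scheduled pre-session record.

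**Step 6: count of procedures.** Table 1 puts no condition on TMS. With 39 participants and 2 batteries each, 39 × 2 = 78 are planned. Those before the window number 39, and 39 / 78 = 50%. Any test done once before and once during treatment gives this share, so it says nothing about risk.

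**The case against.** The strongest reply is that a window starting at first exposure is a legitimate choice in a trial about the safety of repeated ultrasound. The uncovered interval precedes all ultrasound exposure and is the same in every arm, so the comparison of harms between arms is little affected. That stands, and it limits the weight of the point.

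The other side is also right to resist several stronger readings that a reader might infer:

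- *The window contradicts the definition of an adverse event.* It does not. The definition covers "any unfavorable or unintended sign, symptom, or illness occurring in a participant regardless of causal relationship to the study" and adds that "Worsening of preexisting conditions will also be considered adverse events", but it says what counts and sets no dates. The tension is with the withdrawal criteria, which do have a start.
- *There is no pre-treatment symptom record.* There is a partial one. A pain flare after the baseline tests, for example, should show in the diary week.
- *Such events would appear nowhere in the trial's data.* The article condenses protocol version 1.3, which is not shown and may hold recording rules for this interval. The withdrawal criterion itself shows that early events are recognised. The week-1 question may also bring up earlier symptoms, although an onset before the first session lies outside the stated window.
- *Participants are under an unmonitored medication freeze.* The restriction applies in principle only, keeps existing treatment, and allows rescue analgesics and safety exceptions. Nothing is withdrawn.
- *Half of the procedure-related events are missed.* The 50% counts procedures. The article gives no event rate for TMS or sensory testing and excludes people with a history of epileptic seizures, so the number missed is unknown and may be small.

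What survives is narrower. The article fixes the start of scheduled collection, twice and consistently, after study procedures that carry their own possible harms.

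**Conclusion.** The point holds as a modest, easily corrected weakness in safety capture. As written, scheduled collection leaves out events from the week-0 TMS and, in limb pain, sensory testing, together with events arising in the preintervention week. It does so in participants whom the withdrawal criteria already treat as able to have an adverse event.

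The conclusion rests on two readings: that Table 1 and Trial Schedule describe the full collection window, and that allocation precedes the baseline tests as the sentence order implies. If allocation in fact follows those tests, the gap remains, but part of it concerns enrolled participants not yet randomised. The number of missed events cannot be estimated from the article. Nothing here calls the efficacy analysis into question, and the comparison of ultrasound harms between arms is little affected.

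**What to change.** Amend the sentence in Trial Schedule and the adverse-event row of Table 1 so that events are recorded from the first week-0 study procedure (or from consent) through week 16. That adds ticks in the two blank columns. Ask the symptom question already used at each session once more, immediately before session 1. In the report, list events before the first session separately from those after it, for all randomised participants, including any who never receive a session.

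The cost is a protocol amendment, two added collection points in the existing electronic data capture and a few more events to record, with no extra visit. The real limitation is timing. By February 28, 2026, 20 of 39 participants had been enrolled, so from that date at most 39 − 20 = 19 could be covered prospectively, and fewer as enrollment continues. For those enrolled before the change, only retrospective review of source records is possible. The data will then hold two collection windows, and the report should say so.

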**Figure 2. F2:**

Trial schedule. TUS: transcranial focused ultrasound stimulation; W: week.

**Table 1. T1:** Schedule of enrollment, intervention, and assessment.

	Baseline assessment—week 0	Preintervention period	Intervention period								Follow-up period	
			Week 1	Week 2	Week 3	Week 4	Week 5	Week 6	Week 7	Week 8^a^	Week 12	Week 16
Eligibility screen	✓											
Demographic background	✓											
Intervention			✓	✓	✓	✓	✓	✓	✓	✓		
Pain diary^b^		✓	✓	✓	✓	✓	✓	✓	✓	✓		
Pain NRS^c^ and SF-MPQ-2^d^^,^^e^	✓		✓	✓	✓	✓	✓	✓	✓	✓	✓	✓
BPI^f^, EQ-5D-5L, HADS^g^, PCS^h^, and PSEQ^i^	✓									✓		
MMSE^j^	✓									✓		
Motor cortical excitability	✓									✓		
QST^k^^,^^l^	✓									✓		
*Shibire* questionnaire^m^	✓									✓		
*Shibire* NRS^e^^,^^m^	✓		✓	✓	✓	✓	✓	✓	✓	✓	✓	✓
PGIC^n^										✓		
Blinding										✓		
Adverse events			✓	✓	✓	✓	✓	✓	✓	✓	✓	✓
Malfunction of the device			✓	✓	✓	✓	✓	✓	✓	✓		

a If the intervention is discontinued, evaluations are performed at week 8.

b Pain diary is recorded from 1 week before the intervention until 1 week after its completion (week 8).

c NRS: numerical rating scale.

d SF-MPQ-2: Short-Form McGill Pain Questionnaire version 2.

e These measures are assessed immediately after each intervention.

f BPI: Brief Pain Inventory.

g HADS: Hospital Anxiety and Depression Scale.

h PCS: Pain Catastrophizing Scale.

i PSEQ: Pain Self-Efficacy Questionnaire.

j MMSE: Mini-Mental State Examination.

k QST: quantitative sensory testing.

l Assessed if the maximum pain site is located in the upper or lower extremities.

m Assessed if *shibire* is present. “*Shibire*” is a common Japanese term describing abnormal sensations, such as paresthesia, dysesthesia, or numbness, and may also refer to motor difficulty.

n PGIC: Patient Global Impression of Change.

### Sample Size Estimation

Given the exploratory nature of this study, the sample size was not intended to provide a definitive or fully powered estimate of treatment efficacy. As no previous clinical trials have examined the effects of repeated sessions of TUS in patients with chronic pain, the sample size calculation was based on a prior clinical trial of rTMS for NP [8]. In that study, the mean reduction in pain score immediately after the final intervention was 34.8 (SD 15.2) in the active stimulation group (n=15). Assuming that the sham group would experience half of this effect (mean reduction of 17.4) [3,8] and that both active TUS groups in our study would yield the same mean reduction (34.8), the SD was set at 15.2 for all groups. On the basis of these assumptions, a one-way ANOVA with an α of .05 and 80% power indicated that 37 participants would provide a reasonable basis for estimating potential between-group differences. Accounting for a 5% dropout rate, the final target sample size was set at 39 (13 per group). The anticipated dropout rate of 5% was based on a previous rTMS trial conducted by our group in patients with NP, in which the dropout rate was below 5% [8].

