### Outcomes

#### Overview

The primary outcome is the change in weekly average pain intensity scores recorded in a pain diary using an 11-point NRS ranging from 0 (no pain) to 10 (worst imaginable pain). Participants will evaluate their average pain over the previous 24 hours daily at home. Weekly averages will be calculated, and changes from the baseline week to each postintervention week up to week 8 will be assessed. The primary end point is the change in weekly average pain scores from baseline to week 8. To assess clinically meaningful improvements, responder analyses will identify the proportion of participants achieving reductions of 2 points or more and 4 points or more [35] in weekly average pain scores at week 8 compared with baseline.

Secondary outcomes comprise patient-reported and physiological measures, enabling a multidimensional evaluation of pain, functional impact, psychological status, neurophysiological response, and patient perception over time. These include both longitudinal changes from baseline and postintervention assessments across the following domains.

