Demographic characteristics and outcomes will be summarized descriptively, with longitudinal outcomes presented as line graphs over time. The primary analysis will use a linear mixed-effects model for repeated measures (MMRM) to evaluate changes in weekly average pain scores from the pain diary. The model will include change from baseline in weekly average pain scores as the response variable, with treatment group, time point, and their interaction as fixed effects and individual participants as a random effect. Baseline pain scores will be included as covariates. The primary treatment effects will be estimated using model-based contrasts comparing M1 stimulation with sham stimulation and PSI stimulation with sham stimulation at week 8. Multiplicity arising from these 2 primary comparisons will be controlled using the Dunnett adjustment. To identify time points showing significant changes from baseline, the Dunnett multiple comparison procedure will be used, with the baseline week serving as the control. The number and proportion of responders will be summarized by treatment group, and between-group comparisons will be performed using logistic regression models adjusted for baseline pain scores. Missing week 8 pain diary data will be imputed using the last observation carried forward method for responder analyses only. Secondary outcomes measured repeatedly, such as pain NRS and SF-MPQ-2, will also be analyzed using MMRM in the same way as the primary outcomes. Outcomes assessed only at baseline and week 8—including BPI, EQ-5D-5L, HADS, PCS, PSEQ, MMSE, QST, and MEP—will be evaluated using analysis of covariance, with change from baseline as the response variable, treatment group as a fixed effect, and baseline value as a covariate. Paresthesia-related outcomes will be analyzed using MMRM, analysis of covariance, or logistic regression depending on data type and timing. PGIC responses at week 8 will be summarized by treatment group and compared using the Fisher exact test. All analyses will be 2 sided, with *P* values below .05 considered statistically significant.

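### The stated 80% power belongs to a global ANOVA; each of the two Dunnett-adjusted primary contrasts has about 70% on the same assumptions, before any gain from baseline adjustment

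*Protocol article*

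**What the plan says.** The Sample Size Estimation section of the protocol article takes its inputs from an earlier rTMS trial, in which "the mean reduction in pain score immediately after the final intervention was 34.8 (SD 15.2) in the active stimulation group (n=15"). It continues: "Assuming that the sham group would experience half of this effect (mean reduction of 17.4"), and assumes that "both active TUS groups in our study would yield the same mean reduction (34.8"), with one SD of 15.2 for all arms. From these, "a one-way ANOVA with an α of .05 and 80% power indicated that 37 participants" were required. A 5% dropout allowance brings the target to 39, or 13 per group. The same section says that the trial is exploratory and disclaims full power.

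The Statistical Analysis section defines a different primary test. A mixed model for repeated measures, with baseline pain as covariate, yields two week-8 contrasts: M1 versus sham and PSI versus sham. It adds that "Multiplicity arising from these 2 primary comparisons will be controlled using the Dunnett adjustment", and that "All analyses will be 2 sided". The Protocol Amendments section explains that these comparisons and their multiplicity adjustment were spelled out during peer review.

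Under Outcomes, Overview: "The primary end point is the change in weekly average pain scores from baseline to week 8". The scores are daily 0 to 10 ratings averaged over a week.

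**The concern.** The only power figure in the article is attached to a test that is not the primary analysis. A significant three-group F test says that the arms differ somewhere; it does not say which site differs from sham. The trial has two active arms in order to look at the sites separately, and it will judge each against sham at a multiplicity-adjusted 5% level. The relevant figure is therefore the power of each contrast, and it is lower than 80%.

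What is at stake is how a negative site result is read. If one target fails to reach significance, a reader who carries over the 80% will give that result more weight than the design supports, and a useful target could be set aside too readily.

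**Working it through.** **Inputs.** From Sample Size Estimation: mean reductions 34.8, 34.8 and 17.4; SD 15.2; alpha .05; N = 37, raised to 39. From Randomization and Blinding: 1:1:1 allocation. From Statistical Analysis: two two-sided contrasts against a shared sham arm, Dunnett-adjusted.

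**1. The plan's own figure.** The grand mean is 29.0. The variance of the means is (5.8² + 5.8² + 11.6²)/3 = 67.28. Then f² = 67.28/15.2² = 0.2912 and f = 0.540. With noncentrality N × f² and N − 3 denominator degrees of freedom, power is 79.7% at N = 36, 80.9% at 37 (noncentrality 10.77) and 83.3% at 39. So 37 is the smallest N that reaches 80%, and 37/0.95 = 38.9 rounds up to 39. Both published figures reproduce.

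**2. The F test if only one site works.** With means 34.8, 17.4 and 17.4, the grand mean is 23.2 and the variance of the means is (11.6² + 5.8² + 5.8²)/3 = 67.28, as before. Power at 37 is again 80.9%.

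**3. The primary contrasts.** The standardised difference is 17.4/15.2 = 1.145. The noncentrality of one contrast is 1.145/√(2/n), which is 2.84 at n = 37/3 = 12.33 per arm and 2.92 at n = 13. The two-sided Dunnett critical value for two contrasts (correlation 0.5, N − 3 degrees of freedom) is 2.31 at N = 37 and 2.30 at N = 39. Power from the noncentral t and the joint distribution:

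| Evaluable | Global F | Each contrast | Both contrasts | At least one |
|---|---|---|---|---|
| 37 | 80.9% | 70.3% | 56.6% | 84.0% |
| 39 | 83.3% | 72.9% | 59.9% | 86.0% |

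The last two columns assume that both sites work. If only one does, the power for that site's contrast stays at 70% to 73%.

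**4. Size needed for 80% per contrast.** On the same inputs, 15 evaluable per arm falls just short (79.8%) and 16 per arm gives 82.6%. Strictly, that is 48 evaluable against 37.

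**5. Effect of the baseline covariate.** Steps 3 and 4 use the unadjusted SD. If baseline and change correlate at r, the residual SD is 15.2 × √(1 − r²). The article gives no r. As an assumption:

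| r | Each contrast, 37 evaluable | Each contrast, 39 evaluable |
|---|---|---|
| 0.3 | 75% | 77% |
| 0.4 | 78% | 81% |
| 0.5 | 83% | 85% |

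**6. Precision of the SD.** It comes from 15 patients, so the chi-square interval has 14 degrees of freedom: 15.2 × √(14/26.12) = 11.1 to 15.2 × √(14/5.63) = 24.0. Over that range the power of each contrast at 37 runs from 94% to 32%. This uncertainty would affect any sizing method; it is separate from the mismatch in steps 1 to 3.

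**The case against.** The best defence is that the article promises little. It calls the trial exploratory, disclaims full power, names the test behind the 80%, makes no claim about power at a given site, and concedes in the Discussion that small differences may be missed. The chance of at least one significant contrast is about 84% if both sites work, which suits a proof-of-concept aim, and baseline adjustment could bring each contrast to 80%. Most of this stands, and it lowers the severity. It does not remove the point. None of the disclaimers tells the reader that the 80% belongs to another test, the shortfall applies to the large assumed effect of 1.14 SD and not only to small ones, and the gain from baseline rests on a correlation that is not stated.

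A reader might also infer more than the document supports:

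- **That the sample size was miscalculated.** It was not; 37 and 39 both reproduce.
- **That the F test looks better because both active arms are assumed to work.** Step 2 shows the same power when only one works. The F test answers a global question; that is the whole difference.
- **That a 34.8-point reduction, impossible on a 0 to 10 scale, invalidates the power.** A change of units alone leaves the standardised difference of 1.145 as it is. The inputs are from a different measure (post-session ratings, not a weekly diary average), but how the diary SD would compare cannot be judged from the document.
- **That the trial must be enlarged.** Given its stated aim, it need not be.

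**Conclusion.** The point holds as a mismatch between the sizing test and the primary analysis, and should be fixed. The 80% is right for the global ANOVA. On the plan's own means, SD and alpha, each primary contrast has about 70% power at 37 evaluable and 73% at 39, so the assumed effect at a given site would be missed about 3 times in 10 (1 − 0.703 = 0.297). If both sites work, at least one would be missed about 4 times in 10 at 37 (1 − 0.566 = 0.434). These figures rest on equal arms, a common SD of 15.2 and no covariate gain; with an assumed baseline correlation of 0.3 to 0.5, each contrast has 75% to 83% at 37. The exploratory aim keeps this below a must-fix.

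**What to change.** Keep 39 participants and reword the Sample Size Estimation section:

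1. Say that the 80% applies to the global three-group F test.
2. Give the power of the planned tests at 37 and 39 evaluable: about 70% and 73% for each Dunnett-adjusted contrast, 57% and 60% for both, 84% and 86% for at least one if both sites work. Label these as before baseline adjustment; if a gain from the covariate is claimed, state the correlation assumed.
3. State the scale of the 34.8 (SD 15.2) figures, and that they are ratings taken straight after the last rTMS session and not the weekly 0 to 10 diary average. Add that the SD rests on 15 patients (95% CI about 11.1 to 24.0), with per-contrast power of 94% to 32% at 37 over that range.
4. Commit to interpreting each contrast by its estimate and confidence interval, so that a non-significant site is not read as evidence against that target.

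The cost is wording and a less favourable printed figure. No extra patients are needed and no analysis changes.

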### Protocol Amendments

During peer review of this protocol manuscript, the Statistical Analysis section was revised to explicitly specify the prespecified primary treatment comparisons (M1 stimulation vs sham stimulation and PSI stimulation vs sham stimulation at week 8) and the planned multiplicity adjustment.

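### The stated 80% power at 37 participants is that of an omnibus ANOVA; on the same inputs each Dunnett-adjusted primary contrast with sham has about 69-73%, before any gain from baseline adjustment

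*Protocol article*

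**What the plan says.** In the protocol article, Sample Size Estimation takes its inputs from an earlier rTMS trial in neuropathic pain: a mean reduction of 34.8 (SD 15.2) after active stimulation, with sham assumed to achieve half of that, 17.4. It further assumes that "both active TUS groups in our study would yield the same mean reduction (34.8), the SD was set at 15.2 for all groups". From these it concludes that "a one-way ANOVA with an α of .05 and 80% power indicated that 37 participants" are enough, and raises 37 to 39 (13 per arm) for 5% dropout. The same section states that the size was not chosen to give full power for efficacy.

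Statistical Analysis specifies different tests. The primary analysis is a mixed model for repeated measures with baseline pain as a covariate, and the primary effects are "model-based contrasts comparing M1 stimulation with sham stimulation and PSI stimulation with sham stimulation at week 8". It adds: "Multiplicity arising from these 2 primary comparisons will be controlled using the Dunnett adjustment". Testing is two-sided at .05.

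Protocol Amendments reports that, during peer review of the manuscript, the analysis section was "revised to explicitly specify the prespecified primary treatment comparisons" and the multiplicity adjustment. The sample-size section gives a power figure for the ANOVA only.

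**The concern.** An omnibus F test asks whether the three means differ at all. The primary tests ask whether a given site beats sham, at a stricter critical value because there are two of them. Power for the first question does not carry over to the second.

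The article prints one power figure, and a reader could take it as the chance of detecting a given site that works as assumed. If that chance is nearer 70%, a non-significant contrast says less against a site than the article suggests. This matters in a proof-of-concept trial, where such a result may decide whether a target is pursued.

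**Working it through.** **Inputs (Sample Size Estimation; Statistical Analysis).** Means 34.8, 34.8 and 17.4; common SD 15.2; 1:1:1 allocation; two-sided .05; 37 evaluable or 39 randomised. Only the standardised difference enters: d = 17.4 / 15.2 = 1.145 for each active arm against sham.

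**Step 1. Reproduce the plan's figure.** The grand mean is 29.0, and the deviations are 5.8, 5.8 and -11.6. The between-group SD is √[(33.64 + 33.64 + 134.56)/3] = √67.28 = 8.20, so Cohen's f = 8.20 / 15.2 = 0.540. Power comes from the noncentral F with df (2, N - 3) and noncentrality N·f², where f² = 0.2912.

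| N | Noncentrality | ANOVA power |
|---|---|---|
| 36 | 10.48 | 79.7% |
| 37 | 10.77 | 80.9% |
| 39 | 11.36 | 83.3% |

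With whole-number arms at N = 37 the power is 80.4-82.0%, depending on which arm has 13. So 37 is the smallest N that reaches 80%, and 37 / 0.95 = 38.9 rounds up to 39. Both stated numbers are right for the test named.

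**Step 2. Power of the primary contrasts.** For each contrast, noncentrality = 17.4 / [15.2·√(1/n_active + 1/n_sham)], with pooled SD and df = N - 3. The critical value is the two-sided Dunnett value for two comparisons with a common control. At 13 per arm, noncentrality = 1.145·√(13/2) = 2.92 and the critical value is 2.302. Marginal power is from the noncentral t. The joint figures are from simulation with 1,000,000 replicates, which also confirmed the marginal ones.

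| Evaluable | Critical value | Each contrast | Both | At least one |
|---|---|---|---|---|
| 36 (12 per arm) | 2.310 | 68.9% | 55% | 83% |
| 37 (one arm of 13) | 2.306-2.310 | 69.0-70.9% | 56-57% | 84-85% |
| 39 (13 per arm) | 2.302 | 72.9% | 60% | 86% |

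**Step 3. Source of the gap.** An unadjusted contrast would have about 79% at N = 37 and 81.1% at N = 39. Most of the shortfall therefore comes from the Dunnett adjustment.

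**Step 4. Only one site works.** With equal arms, means of 34.8, 17.4 and 17.4 give the same f, so ANOVA power at N = 39 stays at 83.3%. The chance of any Dunnett rejection falls to about 74%.

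**Step 5. Baseline adjustment.** The article gives no correlation between baseline and change, so ρ is an assumption here. The residual SD becomes 15.2·√(1 - ρ²), with one further df lost.

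| Assumed ρ | Each contrast, N = 37 | Each contrast, N = 39 |
|---|---|---|
| 0.2 | 72% | 75% |
| 0.3 | 75% | 77% |
| 0.4 | 78% | 81% |
| 0.5 | 83% | 85% |

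A correlation of about 0.4-0.45 would be needed to regain 80% per contrast.

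**Step 6. For scale.** Without covariate gain, 15 evaluable per arm give 79.8% per contrast and 16 give 82.6%.

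**The case against.** The strongest reply is that the article never promises 80% for each site. It says the size was not meant to give full power, presents 37 as a reasonable basis for estimating differences, and lists possible lack of power as its first limitation. Under its own scenario, with both sites working, the chance of at least one significant contrast is 84-86%. That is a defensible criterion for an exploratory two-site trial, and the article names no other. All of this stands and limits the weight of the point. It does not remove the mismatch. The limitations paragraph warns only about subtle differences, whereas the shortfall here is at the assumed effect of d = 1.145. The at-least-one figure also depends on both sites working, and the design includes two sites partly to look for differences between them.

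A second reply is that the mixed model with a baseline covariate may recover the loss. It may, as Step 5 shows, but the sample-size section assumes no such gain. Equally, 69-73% is not the exact power of the planned model, and any new wording must say so.

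Three stronger readings are tempting and should be resisted. A reader might infer that the sample-size arithmetic is wrong; Step 1 shows that it is not. A reader might infer that no omnibus test will ever be run; the analysis plan is not shown and the models carry a three-level group factor, so one can say only that no omnibus test is named as primary. A reader might infer that the primary comparisons were changed in peer review; Protocol Amendments says only that comparisons already prespecified were made explicit.

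**Conclusion.** The point holds as a mismatch between the test used for sizing and the tests used for inference. The 80% is a true property of the omnibus ANOVA and not of either primary contrast. On the article's inputs each contrast has about 69-71% power at 37 and 73% at 39, and both together about 57-60%. At least one reaches about 84-86% if both sites work, and about 74% at 39 if only one does.

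These figures rest on the assumed means and common SD, near-equal arms, a single week 8 comparison with pooled SD, and no gain from baseline adjustment or the repeated-measures model. Given the declared exploratory aim, the correction is modest. A reader might conclude that the trial is too small and must recruit more; the article sets no per-contrast target, so it does not support that.

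**What to change.** Keep the target at 39. Keep the ANOVA sentence, since it records how the number was chosen, but label it as the basis for N. Then add, for example:

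> For the Dunnett-adjusted primary contrasts with sham, under the same assumptions and ignoring any precision gained from baseline adjustment, 37-39 participants give about 70-73% power for each contrast, about 85% for at least one if both sites are effective, and about 57-60% for both.

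The cost is wording only: no extra participants and no change to the analysis. The downside is that the quoted power becomes less favourable.
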